## Abstract

**Background:**

Substance abuse is the actual psychosocial harm, especially in young people confronted with content marketing in nowadays media environment, a risk factor for experiencing substance abuse. Based on the literature review, education designed based on the cognitive-behavioral model and planning models, such as using a social marketing framework, is the most effective method to prevent addictive substance abuse. Also, media literacy related to substance abuse and the prototype willingness model is considered a new integrated approach to present the intervention measures’ desired results.

**Methods:**

The present study evaluates an intervention program based on media literacy on substance abuse prevention among students using an integrated social marketing approach. This study aims to complete the SMART model’s sixth and seventh stages, implementing intervention and evaluation. Participants will be students of Hamadan University, Iran. Randomization will occur at the university and school levels, and gathered data will appear at two-time (i.e., pre-test and three months follow-up). Intervention group students will obtain both substance abuse prevention education and substance abuse media literacy (SAML) education between pre-test and 3 months post-test. Students in the delayed intervention will be given this education after study accomplishment; this group will receive their regular courses except for substance abuse prevention and media literacy titles during education intervention. The outcome variables are intentions and substance abuse behavior based on prototype willingness and substance abuse media literacy.

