### Sample size and eligibility criteria

According to previous studies, the intervention’s minimum effectiveness is 20% [35–37], referring to changes in the PMW construct, behavior, and SAML. Also, because of considering these cultural differences in the intervention’s minimum level of effectiveness, 20% was considered for intervention effectiveness based on the previous study with the same field and approach; taking into account the clustering coefficient of 1.5, alpha 5%, and 90% desired power, we need 54 people per group. Also, considering the 20% probability of attrition in the intervention process, the present study’s sample size was 116, including 58 in the experimental group and 58 in the control group.$$n=\frac{\overline{p}\left(1-\overline{p}\right){\left({Z}_{\beta }+{Z}_{\alpha /2}\right)}^2}{{\left({p}_1-{p}_2\right)}^2}$$

Inclusion criteria were access to the internet and social media apps (such as WhatsApp, Telegram, and Instagram), being a student in one of the universities in the city of Hamadan, and willing to participate in the study. Before participation, students signed written informed consent forms to participate in this study. The Principal Investigator will access consent forms of student participant data that will be nameless. Also, according to the consent form, students were free to withdraw from the study at any time.

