### Participant characteristics

Subjects were enrolled in this study in 2 plans: university schools and students. It should be noted that Hamadan city is located in the west of Iran. It has 4 state universities, including Bu-Ali Sina University, Hamadan University of Medical Sciences, Hamadan University of Applied Sciences and Technology, and the Hamadan University of Technology. Moreover, it has some non-governmental universities, such as Hamadan Islamic Azad University and Hamadan Payame Noor University [38]. Students were selected by simple random sampling using their ID codes. Thus, students in the cluster in the university, once they are categorized into their stratum, then they are randomized to either the intervention or the control groups.

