### Processes

#### Schools of university

First, university permission to conduct the study was obtained. University administrators would access questionnaires for an estimate if demanded. Efforts were made to balance the inclusion of both state and non-state universities, as well as to range in their socio-demographic characteristics. Based on the previous formative research [27] and random sampling of Hamadan universities, 3 universities were expected to participate. Therefore, the number of students in each school or university was obtained by proportional assignment of students to the school (i.e., the school with the largest number of students, the largest number of students assigned). After coordinating with university officials, the research units were rationed. Then, the samples were randomly collected.

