#### Randomization

Randomization was performed using a stratified random sampling procedure; individuals were assigned to 2 intervention and control groups. Randomization was performed after students signed informed consent, as well as the approval of universities to perform the study.

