#### Statistical methods

Data were analyzed with SPSS version 23 (SPSS Inc., Chicago, Ill., USA) using analysis of variance (ANOVA), independent *t*-test, and other tests. Generally, if the mean score of variables before the intervention was significantly different between the intervention and control groups, the ANOVA test was used; otherwise, we used an independent *t*-test. The independent samples *t*-test (or the Mann-Whitney *U* test) was used to determine differences in numerical variables between the intervention and control groups. To draw a within-group comparison, we used the paired-sample *t*-test or its nonparametric equivalent, the Wilcoxon test. If necessary, missing data were examined at each time point and handled with an appropriate imputation method. All data of the full protocol and intervention study were potentially shareable after unidentified individuals. All researchers could access the data upon request to the Vice-Chancellor for Research and Technology of Hamadan University of Medical Sciences.

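### The abstract and the body disagree on the unit of randomisation, and the named tests use neither the clustering the trial was sized for nor the strata it randomises within

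*Protocol article*

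**What the plan says.** The protocol article describes the allocation in two ways.

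- **Abstract, Methods:** "Randomization will occur at the university and school levels".
- **Randomization section:** "Randomization was performed using a stratified random sampling procedure; individuals were assigned to 2 intervention and control groups". The same section places this step after students had signed consent and universities had agreed.
- **Participant characteristics:** students are grouped first and, "once they are categorized into their stratum, then they are randomized to either the intervention or the control groups". The stratum is not defined.
- **Blinding description:** participants are divided between the arms after consent.

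Two other sections bear on the design.

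- **Sample size and eligibility criteria:** "taking into account the clustering coefficient of 1.5, alpha 5%, and 90% desired power, we need 54 people per group".
- **Schools of university:** "3 universities were expected to participate", with student numbers shared across schools in proportion to size. The number of schools is not given.

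Statistical methods names the between-arm tests. The independent t-test or Mann-Whitney test "was used to determine differences in numerical variables between the intervention and control groups", and ANOVA replaces the t-test where baseline means differ significantly. Nothing named there has a term for university, school, cluster or stratum.

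**The concern.** The unit of randomisation decides which analysis is valid. If universities or schools were allocated, students in the same unit share an arm and resemble one another, so a test that treats them as independent understates the standard error. If individuals were allocated within strata, the arms are balanced on the strata by design, and a test that ignores them overstates the standard error. The two errors run in opposite directions, so the reader cannot judge the planned p-values without knowing which design was used.

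The sample size adds to the doubt. It allows for clustering, which the named analysis then ignores. If individuals were randomised, the allocation itself gives no reason for the allowance, and no other reason is stated.

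**Working it through.** **Inputs from the protocol (Sample size and eligibility criteria).** Clustering coefficient 1.5, read here as a design effect (DE); alpha 5%, two-sided because the printed formula uses Z at alpha/2; power 90%; effect 20%; 54 per group; 116 in total.

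**Assumed input.** The share r of outcome variance that lies between strata is not given. I use 5%, 10% and 20%.

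**The plan's own figure.** The 54 per group cannot be reproduced, because the two proportions are not stated. With (1.960 + 1.282)² = 10.507 and a difference of 0.20, the printed formula multiplied by 1.5 gives 54 only if the mean proportion is about 0.16; without the 1.5 it gives 54 only at about 0.29. So the figure does not show how the 1.5 was applied. That is a separate matter and does not affect the steps below.

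**Reading 1: individuals randomised within strata.** The true variance of the arm difference is (1 − r) times what the unadjusted test assumes.

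- Type I error = 2[1 − Φ(1.960/√(1 − r))].
- Power, where a stratum-adjusted analysis would have 90% = Φ(3.2415 − 1.960/√(1 − r)), with 3.2415 = 1.960 + 1.2816 before rounding.

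| r (assumed) | 1.960/√(1 − r) | Type I error | Simulated | Power |
|---|---|---|---|---|
| 5% | 2.011 | 4.4% | 4.1% | Φ(1.231) = 89% |
| 10% | 2.066 | 3.9% | 3.8% | Φ(1.176) = 88% |
| 20% | 2.191 | 2.8% | 2.8% | Φ(1.050) = 85% |

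The simulation ran t-tests on 116 students in three strata, 6,000 runs per setting. On this reading the randomisation itself calls for no design effect; if 1.5 was applied as a multiplier, 54 without it is 54/1.5 = 36 per group.

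**Reading 2: schools or universities randomised.** The true variance is DE times what the unadjusted test assumes.

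- Type I error = 2[1 − Φ(1.960/√1.5)] = 2[1 − Φ(1.600)] = 0.1095, about 11%.
- Simulated t-tests with DE held at 1.5 and 4 to 20 clusters gave 10.7% to 11.6%.
- The 54 per group carry the information of 54/1.5 = 36 independent students.

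**The case against.** The strongest defence is that the conflict is mostly one loose sentence in the abstract. Three sections of the body allocate individuals or participants, two of them explicitly after consent, and equal arms of 58 would be hard to reach by allocating three universities of unequal size. The abstract may simply be describing how universities and schools were sampled. On that reading an unadjusted t-test keeps its error at or below 5%, and the loss is one of precision only. This stands, and it sets the size of the point.

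The defence also holds that the 1.5 need not signal a cluster trial. Multistage sampling is often given a design effect, and delivery through group chat rooms could create clustering within the intervention arm even when individuals are randomised. That stands too: the fault is that the 1.5 is unexplained, not that it is necessarily wrong.

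A third argument, that a stratum term is detail for a separate analysis plan, carries less weight. The article does name the tests and the rule for choosing between them; its closing reference to other tests supplies no cluster or stratum term.

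A reader might infer more: that the t-tests are invalid on either design, that the true error could reach 25%, or that only one degree of freedom is available (critical t 12.7). The documents do not support these. The first fails for individual allocation. The 25% needs an intracluster correlation of 0.05, which is not in the protocol, and three universities of equal size, although numbers are proportional to size. The single degree of freedom applies only if the three universities were the allocated units, whereas the abstract also mentions schools and their number is unknown.

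**Conclusion.** The contradiction is real and has to be resolved, and the named tests do not reflect the design on either reading. The consequences differ.

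- **Individual allocation within strata, the better supported reading:** the tests are valid but conservative. True error is about 4.4% to 2.8% and power about 89% to 85% instead of 90%, if strata explain an assumed 5% to 20% of outcome variance.
- **Allocation of schools or universities, the less supported reading:** a nominal 5% test has a true error of about 11%. This rests on the stated 1.5 being a design effect.

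The documents do not settle which was done. Unless whole schools or universities were allocated, this is a clarification with a modest cost in precision, not a flaw that invalidates the comparison.

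**What to change.** 1. Confirm from the allocation records what was randomised and state that one unit throughout. If individuals were allocated, correct the abstract.
2. Name the stratification variable or variables, which the text leaves undefined, and include them as a term in every between-arm model. If school strata are sparse among 116 students, use university alone.
3. State what the 1.5 covers, for example group chat-room delivery or a deliberate conservative margin, or drop it from the calculation. If it stands for chat-group clustering, note that a stratum term does not address that.
4. If whole schools were allocated, report the number per arm and replace the t-tests with a mixed model with a school random intercept and small-sample degrees of freedom, or with a cluster-level analysis.

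The cost is a wording correction and one model term. The Student measures section already lists university and school among the items collected, so no new data are needed. Only step 4 changes the analysis substantially, and only if schools were allocated.

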**Discussion:**

Evaluation of Substance abuse prevention and substance abuse media literacy education must be careful to ensure that they effectively enable people, especially in youth in the new media ecology and unique “Infomedia” ecosystems, in the current digital society. The SAML education plan’s evaluation has the first web-based education program in universities. No prior research has psychometrically considered SAML in students in the SMART model’s sixth and seventh stages.

**Trial registration:**

IRCT20200914048719N1. Registered on June 30, 2021.

## Background

According to the United Nations Office on Drugs and Crime (UNODC), in 2017, a total of 271 million people aged 15 to 64 years were drug abusers [1, 2]. In this regard, Iran mainly deals with this social, political, and global problem due to its young population and geographical location [3]. Epidemiological studies suggest an average age of 17.8 ± 3.9 years for the onset of the first use of addictive drugs, which gradually increases with age. This age group is associated with young people’s entry into universities and starting the studentship period. The first year in a university is considered the most challenging time for students. This period includes social challenges of being away from families, meeting new friends with different cultures, and mental challenges (such as successfully performing multiple assignments). In turn, it can lead to mental disorders (such as depression) and increase the possibility of addictive drug abuse, loneliness, and estrangement [4].

On the other hand, previous studies have reported that young people are the most popular social media platform users [5, 6]. Also, the media have become a global culture in youth’s lives. These new opportunities facilitate access to social interaction and learning [7] while exposing them to environmental risk factors for youth’s health, including having a sedentary lifestyle [8] or lower life satisfaction [9], anxiety, sleep disturbance, [10], and stress [11]. The amount of time spent on the media is associated with addictive substances. The likelihood of substance abuse increases with exposure to images and media content on substance abuse, such as movies and clips [12–14]. In this regard, understanding the harms and functions of the media and cyberspace and acquiring media literacy and learning skills for critical analysis of media messages are the most essential and useful requirements to prevent risky behaviors such as substance abuse, smoking, and unsafe sexual activity [15].

Education must be moral and based on defined theories and models to achieve useful and practical results. Among the ideas and models that are systematically used as a framework and roadmap for the educational process and goals to change behavior are planning models. The social marketing approach, in addition to analyzing successes and failures, provides the necessary guidance for reviewing and educational diagnosis. It also provides educational planning and intervention design methods, facilitates evaluation, and reduces the confusion of educational intervention designers [16]. Dann sees social marketing to promote positive behaviors and abandon negative behaviors [17, 18]. According to the 2002 definition, social marketing means “the customer-centric application of marketing principles and techniques to the development of programs, interventions, and evaluations to change or modify health behavior” [17–19].

Social marketing is a strategy to correct social behaviors. The 2 education strategies and coercion can be used to promote healthy actions and correct high-risk behaviors, including substance abuse.

The social marketing model was selected as a conceptual framework and appropriate research planning by reviewing the patterns and theories of changing individual and collective behavior. Social marketing has been used in various studies to influence various topics (such as tobacco prevention and promoting smoking cessation and alcohol reduction in women and students) [17, 20] and health problems (such as addiction and substance abuse) [20].

The prototype willingness model (PWM) is a model reflected in substance abuse, tobacco, and health risk decision-making, especially in youth and adolescents. PMW proposes behavioral intention, an intermediate variable named behavioral willingness. Behavioral willingness is measured by this essential question “how they react to risky behaviors in a certain social condition.” Besides intention and behavioral willingness, this model contains other variables. When individuals have a positive attitude toward high-risk decision-making and are more attracted to essential factors, they will be more willing to carry out dangerous behavior. According to PWM, individuals have prototypes that play a role in high-risk behaviors (Fig. 1) [21].

**Fig. 1 Fig1:**
[figure not shown]
The PWM model

Media literacy will be added to PWM as a background factor. It will be examined as extended PWM; thus, the media is a background factor in forming the positive and negative prototypes of youth and adolescents. Strong evidence suggests the role of social networking sites in alcohol use [22], showing that youth exposed to alcohol media content on social networking sites increase their alcohol consumption, engage in heavy drinking, and show positive attitudes toward alcohol use [23]. In a similar vein, studies have found that 25–37% of youth post details about their alcohol drinking, which may give younger adults and adolescents the impression that substance abuse is a common behavior among peers of the same age [24, 25]. Accordingly, regarding the prevalence of substance abuse in universities and its negative consequences [26] (e.g., decreased academic motivation, academic failure, physical and mental illness, suicide), as well as conducting a comprehensive study in this field and identifying factors influencing the tendency to use drugs in students, this study’s main objective was to evaluate the effectiveness of substance abuse media literacy (SAML) education and substance abuse education prevention in students. This media literacy intervention was intended to provide and develop skills to analyze and interpret risky content in social media apps (such as WhatsApp, Telegram, and Instagram) and social networking sites because this new medium may also overrepresent media messages about substance abuse [27–30].

### Social media literacy concerning substance misuse and substance abuse media literacy

Social media literacy and SAML concepts have recently emerged as a distinct sub-discipline of media literacy. As a result of the interactive nature of SNSs, these concepts of media literacy include the capacity to reflect on one’s online behavior [31, 32].

Notably, SAML has four dimensions (Purpose, Constructed-ness, High sensation-seeking audiences, Format, Filter & omit) [27, 29] which are different from the content dimensions of social media literacy: the self, medium, and reality [33].

Both of these concepts demonstrate the ability to locate individuals in the connections between the media and actual worlds, be conscious of the exchanges between the self and the media, and distinguish the values of these exchanges [33].

On the other hand, substance abuse media literacy is the skill to analyze and interpret substance use content in social media apps; this skill prevents youth from encouraging them to develop unhealthy tendencies concerning substance use [32]. Both concepts include SAML and social media literacy have the same goal; empowerment of youth to new media risky contents encounter but with different content dimensions.

The study will also assess process evaluation. However, no information is available about aspects of media literacy about substance abuse in Iran. Therefore, this study aimed to evaluate an intervention program based on media literacy on preventing substance abuse among students using an integrated approach to social marketing. Therefore, a randomized, controlled clinical trial study with a parallel-group design of students was performed in the present study.

## Methods/design

### Aim, design, and setting

The study design evaluated web-based randomized controlled trial substance abuse prevention and SAML education programs. It was expected that 3 universities (including Hamadan University of Medical Sciences, Hamadan Islamic Azad University, and Bu-Ali Sina University) would take part in the study. Data were collected from students at 2-time points (i.e., pretest and 3-month follow-up). Interventional research was based on the Social Marketing Assessment and Response Tool (SMART) pattern.

SMART is the operational model of social marketing in the field of health, which is used to improve the behavior of society and includes 4 stages as follows: (1) preliminary planning, (2) formative research (customer analysis, market analysis, and channel analysis), (3) production of interventions, materials, and pretests, and (4) intervention and execution (Fig. 2).

**Fig. 2 Fig2:**
[figure not shown]
SMART

The above outcomes will be obtained in the experimental study.

It should be noted that in this model, previous formative research (including qualitative and descriptive studies) was performed to complete steps 1 to 5 of the SMART model to determine the type of intervention and products (including getting detailed information about audience peculiarities, behavioral market, and communication channel by audience analysis, market analysis, and channel analysis). In a qualitative study, the audience needs and desires were identified, and behavioral market determinants (such as partners and components of the marketing mix and channels) were specified. An effective communication strategy was developed, which was the result of this study. Notably, based on this previous formative-mixed methods research, the substance abuse prevention intervention was considered more accurate, and this intervention was developed based on the most prevalent addictive substances in college students. Also, media literacy intervention would benefit from greater detail based on this previous formative research.

Here are 3 questions to which formative research provided answers: (1) what is the most commonly used substance on college campuses? (2) Which university has a higher prevalence of drug abuse? (3) Which behavioral and non-behavioral factors are involved in the health problem? To answer these questions in the descriptive study, which is a quantitative part of the formative research, students’ demographic information and drug use behavior were assessed based on PWM and media literacy related to substance abuse. The analysis of the qualitative and quantitative parts of the formative research identified the main components of the intervention.

Therefore, based on the results of this formative research, the most commonly used substance on college campuses was marijuana in Hamadan universities. Also, behavioral and non-behavioral factors involved in substance abuse behavior (such as the role of parents, friends, and SAML on risky behaviors) were identified.

Notably, this study (protocol study) was performed to complete the SMART model’s sixth and seventh stages, including the implementation of intervention and evaluation.

It was anticipated that up to 116 students might take part in the study. This study would have taken place during the 2020–2021 school year. Additionally, program completion and feedback on process evaluation (satisfaction, availability, and quality of material education) would be gathered from the intervention students. The research team used the Standard Protocol Items: Recommendations for Interventional Trials (SPIRIT) checklist to prepare this study [34].

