### Measures

#### Student measures

Students completed questionnaires at 2-time points: a pretest and a 3-month follow-up (Fig. 1). The student questionnaire, containing approximately 100 items, covered substance abuse behavior based on PWM variables outcomes (e.g., attitudes, normative beliefs, behavioral intentions, and willingness), self-reports of the SAML Scale (SAMLS), and process evaluation. In addition, demographic questions comprised age, education level, socioeconomic status, sex, gender, parental education level, marital status, name of university, schools and courses, history of smoking and alcohol consumption, addiction status in parents, close friends, substance abuse status, internet access, amount of social media exposure and use of social media, and motivation to use social media.

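### The named between-group tests do not adjust for baseline predictors that the trial itself identifies and collects, which gives up some precision but does not bias the test

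*Protocol article*

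**What the plan says.** Three parts of the protocol article bear on this.

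- **Known factors.** The formative-research account under Aim, design, and setting reports that "behavioral and non-behavioral factors involved in substance abuse behavior (such as the role of parents, friends, and SAML on risky behaviors) were identified". The Background, citing literature, adds: "The amount of time spent on the media is associated with addictive substances".
- **Data collected.** Under Student measures, the questionnaire covers "addiction status in parents, close friends, substance abuse status, internet access, amount of social media exposure and use of social media". On timing: "Students completed questionnaires at 2-time points: a pretest and a 3-month follow-up". The predictors are therefore available at baseline.
- **Analysis.** Statistical methods sets this rule: "Generally, if the mean score of variables before the intervention was significantly different between the intervention and control groups, the ANOVA test was used"; otherwise an independent t-test applies. The t-test or the Mann-Whitney test "was used to determine differences in numerical variables between the intervention and control groups". Neither ANCOVA nor regression is mentioned, although the opening list of methods is left open-ended.

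On allocation, the Randomization section states: "Randomization was performed using a stratified random sampling procedure; individuals were assigned to 2 intervention and control groups". It names no strata. The neighbouring sections mention only university and school, so nothing shows that the arms are balanced by design on parents' or friends' status.

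**The concern.** Outcome variance that a baseline predictor explains stays in the error term of an unadjusted test. The confidence interval is then wider, and the power lower, than the collected data allow. With about 58 students per arm, the arms can also differ by chance in how many students have a close friend or a parent with an addiction, and the unadjusted difference carries that imbalance.

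The rule's only response to imbalance is triggered by the pretest score, so imbalance in these predictors triggers nothing. The response is also empty as written: with two groups and no covariate, one-way ANOVA is the t-test (F = t²). If ANCOVA was meant, it would still adjust for the pretest score only, and only when a baseline significance test happened to reject.

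**Working it through.** **Plan's own figure.** The article gives no precision or power figure for an adjusted analysis. Its sample size (54 per group, 58 after allowing for attrition) is based on a difference in proportions, and p1 and p2 are not stated. It is used here only for arm size and, in step 4, as a 90% power anchor.

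**Inputs from the document:** 58 per arm; two-sided 5%; 20% attrition, which leaves 58 × 0.8 ≈ 46.

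**Assumed inputs:** effect d = 0.5 SD; correlation ρ of pretest with follow-up score 0.5 (0.3 and 0.7 as checks); share q of the variance left after the pretest score that the three covariates explain, 2 to 10%; 30% of students with a close friend who uses. The power figures treat students as independent and ignore the article's clustering coefficient of 1.5.

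**1. Unadjusted test.** Noncentral t, df = 2n − 2, noncentrality d√(n/2). Power is 76.1% at n = 58 and 66.0% at n = 46.

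**2. Add the pretest score.** The effective effect is 0.5/√(1 − 0.5²) = 0.577, with one df fewer. Power is 86.9% at n = 58 and 78.2% at n = 46. The pretest score alone adds 10.8 points at n = 58.

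**3. Add the three covariates.** The effective effect is 0.577/√(1 − q), with three more df deducted.

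| q | effective d | power, n = 58 | gain over step 2 | power, n = 46 | gain over step 2 |
|---|---|---|---|---|---|
| 0 | 0.577 | 86.9% | 0.0 | 78.2% | 0.0 |
| 0.02 | 0.583 | 87.6% | 0.6 | 79.0% | 0.8 |
| 0.05 | 0.592 | 88.5% | 1.6 | 80.2% | 2.0 |
| 0.10 | 0.609 | 90.1% | 3.2 | 82.3% | 4.1 |

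Gains are taken before rounding. For q from 0.02 to 0.10 at n = 58, the gain is 0.8 to 4.0 points if ρ = 0.3 and 0.3 to 1.4 points if ρ = 0.7. If the covariates explain nothing, the loss is below 0.1 point.

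**4. Cross-check on the article's anchor (54 per group, 90% power).** Power = Φ((1.960 + 1.282)/√(1 − R²) − 1.960). For R² = 0.02, 0.05 and 0.10 this gives 90.6%, 91.4% and 92.7%, a gain of 0.6 to 2.7 points.

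**5. Chance imbalance.** The SD of the between-arm difference in a 30% covariate is √(2 × 0.3 × 0.7/58) = 0.085, so a difference of 10 points or more has probability of about 0.24. If the covariate explains 10% of outcome variance, its effect is √(0.10/0.21) = 0.69 SD and a 10-point imbalance moves the estimate by 0.069 SD. At 5% the effect is √(0.05/0.21) = 0.49 SD and the shift 0.049 SD. The standard error of the unadjusted difference is √(2/58) = 0.19 SD.

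**6. Validity of the unadjusted test.** In simulation (58 per arm, 20,000 runs, no treatment effect), the t-test that omits a covariate explaining 5%, 20% or 40% of the variance rejected in 4.7%, 4.9% and 4.8% of runs. The nominal level holds.

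**The case against.** The strongest objection is that a covariate list is ordinary analysis-plan content, that only a condensed article is at hand, and that its list of tests is open-ended. This stands in part. It can be said only that none of the *named* tests uses these covariates; a reader might infer that no analysis at all will use them, and the article does not show that. But the article goes beyond silence. It fixes a rule for the between-group comparison, and that rule can be judged as written.

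Second, the formative research served to design the intervention. It calls these factors involved in substance abuse and gives no strength of association. A reader might take them as established drivers of the outcome scores, which the text does not support. Recorded addiction status is a proxy for the role of parents and friends, the media-time statement is background literature, and nothing links parents or friends to the SAML score in particular. This stands, and it is a reason to keep the expected gain modest.

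Third, pretest attitudes, norms and willingness may already carry much of what friends and parents contribute, so the increment could be close to zero. This also stands. Measuring the gain from a test without the pretest score would overstate it: at 58 per arm, an R² of 20% appears to raise power from 76% to 85%, but most of that range is open to the pretest score alone.

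Fourth, the randomisation strata have a stronger claim to a place in the model than questionnaire items. This is accepted and is part of the fix.

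**Conclusion.** The point holds as one of efficiency. The named tests leave out baseline predictors that the article links to substance use and already collects. Beyond the pretest score, the three covariates probably add about 1 to 3 points of power at 58 per arm, given d = 0.5, a pretest correlation of 0.5 and 2 to 10% of the remaining variance explained. None of these three inputs is in the documents. Most of the benefit of the proposed model comes from the pretest score.

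A reader might infer that the unadjusted result would be biased or its type I error inflated. The documents do not support that. Under individual randomisation, which the Randomization section describes, chance imbalance is already covered by the error rate of the test, and a 10-point imbalance would shift the estimate by only about a third of a standard error (0.069/0.19). The abstract instead places randomisation at university and school level. If that governed, the figures here would not carry over.

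The change is worth making because it costs almost nothing and replaces a rule that does not adjust when it is meant to.

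**What to change.** In Statistical methods, replace the rule that depends on baseline significance with one prespecified linear model (ANCOVA) for each PWM and SAML follow-up score. It should contain:

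- group;
- the pretest value of the same score;
- the randomisation strata, which the text should name;
- close friends' addiction status, parents' addiction status and amount of social media exposure, with their coding fixed in advance and included whatever their baseline p-values.

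Report the adjusted mean difference with its 95% confidence interval, and keep the unadjusted comparison as a supporting result. Fixing the covariates beforehand also prevents later selection from a questionnaire of about 100 items.

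The cost is a sentence or two in the protocol and one model in the SPSS version already planned, with no new data and no more participants. It uses one degree of freedom for the pretest score, three for the covariates if each enters as a single term, and a few for the strata (two if the stratum is the three universities).
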